### Randomization and dosimetry

A researcher not involved in the study will divide the patients into three groups by randomized order (Minitab 16, EUA). Then, opaque envelopes randomly containing information about application of photobiomodulation, photodynamic therapy or corticosteroid will be labelled with sequential numbers. The researcher responsible for treatments will open the first envelope and perform the procedure written therein. The internal contents will be revealed only after statistical analysis.

The dosimetry to be used in this study is based on a pilot clinical study performed by our group, which followed the recommendations from ASLMS [21]. In brief, the aim was to compare the effects of PBM and topical corticosteroid in VLS evaluating clinical response, itching, skin thickness (atrophy), and recurrence of disease after treatments. The study was prospective, randomized, and controlled in 20 women. CAAE number of Research Ethics Committee: 34,715,314.6.3001.0069. Corticosteroid group: clobetasol propionate 0.05% ointment applied once daily at a dose of 1 g/application for 4 weeks. PBM group: methylene blue 0.01% intralesional, laser λ = 660 nm, *P* = 100 mW, *I* = 510 mW/cm^2^, E = 4 J, exposure radiant = 20 J/cm^2^, *t* = 40 s, once a week for 4 weeks. The variation in intensity of itching was compared between groups, the corticosteroid group reduced the itching at 83.75%, and the PB group decreased 50.00%. The corticosteroid group showed significant variation in the skin thickness relative to PB (*p* = 0.006). This group had a reduction in thickness of the skin −27.51%, while in PB group showed an increase of 49.07%. The treatments were completed in December 2014 and until the month of September 2015 in the corticosteroid group there was 7 patients with no symptoms, while in the PB group there was 6 patients. In the corticosteroid group, the first recurrence was two months after the treatment, while the PBM was only 4 months later.

The groups to be studied and their dosimetry are showed at Table 1.

**Table 1 Tab1:** Characteristics of the groups

Group	Number	Treatment	Parameters
GC	20	Corticosteroid over the whole vulva	Clobetasol propionate 0.05% ointment applied once daily at a dose of 1 g/application (1 g sachets) for 4 weeks

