### Statistical evaluation

Using the G* Power software version 3.1.9.2, the calculus of power analysis was determined by choosing F tests for repeated measures, within-between interaction, since 3 groups will be studied, and each group will be measure before and after treatments. The effect size was determined using the formula [26]:$$ d=\frac{largest- smallest}{{\left(\frac{\sigma }{\sqrt{n}}\right)}^2} $$

The largest and smallest mean values, as well as the standard deviation were taken from the pilot clinical study [21]. The α error was set at 5% and the β error was set at 95%. The n value is the number of groups, i.e., three. According to the G* Power, a sample of 20 patients per group will be required for a power of 88.7%.

The profile of patients will be analyzed according to age, duration of disease, comorbidities and reported symptoms. A descriptive analysis will be conducted and presented by graph.

The clinical, histological, immunohistochemical, and spectroscopic findings will be submitted to inferential statistical analysis to verify the differences between the treatment groups. Associations between these results will also be analyzed. The significance chosen for the tests will be 95%.

First, the statistical distribution of the data will be evaluated. If the data conform to a Gaussian curve, parametric tests will be used. Graphs will be constructed in accordance with the means and standard deviations of the data.

However, if the data is unsuitable for a normal distribution, they will be analyzed with nonparametric tests. Box-type and quartile graphs, constructed according to the median of the results, will be used to present the data.

All data analysis will be performed using SPSS 22 Statistics software (IBM, USA).

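### Fix one baseline-adjusted analysis per outcome in advance: ANCOVA on the day-30 value uses the baseline better than the two-time interaction and removes the normality-driven choice of test

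*Protocol article*

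**What the plan says.** Under Statistical evaluation, the power calculation was made in G*Power by "choosing F tests for repeated measures, within-between interaction, since 3 groups will be studied, and each group will be measure before and after treatments". With alpha at 5%, the result is that "a sample of 20 patients per group will be required for a power of 88.7" per cent.

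The analysis itself is described only in general terms. All four families of findings (clinical, histological, immunohistochemical, spectroscopic) go to inferential tests of differences between groups. The distribution is examined first, and Gaussian data lead to parametric tests. Then: "However, if the data is unsuitable for a normal distribution, they will be analyzed with nonparametric tests". Neither branch names a test, a contrast or a covariate.

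The baseline data needed for adjustment will exist. The Clinical subsection gives the corticosteroid group readings on the first and 30th day, and the two light-therapy groups are measured weekly over the same 30 days. The spectroscopy subsection gives the corticosteroid group a baseline and a 30-day spectrum. The Histological subsection has biopsies at baseline and at 30 days in every patient.

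**The concern.** There are two linked weaknesses.

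- **Efficiency.** The test behind the sample size corresponds to an analysis of change scores. This fixes the coefficient of the baseline at 1. ANCOVA estimates that coefficient and has smaller residual variance whenever the baseline/day-30 correlation is below 1. With 20 patients per arm, that precision is worth having.
- **Pre-specification.** The rule lets the trial data select the kind of test. At n = 20 a normality check is close to chance for moderately non-normal outcomes. Itch, skin clamping, lesion area, histology scores, seven immunohistochemical markers and reflectance could then fall on different branches and give results that cannot be compared. The nonparametric branch also permits a comparison of day-30 values alone, which can lose much of the planned power.

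**Working it through.** **Inputs from the article:** 3 groups (k = 3), 2 measurements (m = 2), N = 60, alpha 0.05, stated power 88.7%. **Not in the article:** the effect size f, the standard deviation, and the baseline/day-30 correlation ρ. The article says "The largest and smallest mean values, as well as the standard deviation were taken from the pilot clinical study" but prints none of these values, and the pilot itching result is given without a standard deviation. So ρ is assumed, over the range 0.3 to 0.9.

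**Step 1: the stated figure.** In the G*Power form, λ = f²·N·m/(1 − ρ), df1 = (k − 1)(m − 1) = 2 and df2 = (N − k)(m − 1) = 57. Without f or ρ, 88.7% cannot be derived forward. Solving backward, 88.7% needs λ = 12.80, that is f = 0.273 at ρ = 0.3, 0.231 at ρ = 0.5 and 0.179 at ρ = 0.7. Check: 0.231² × 120 / 0.5 = 12.8. The stated power is attainable but cannot be verified from what is printed.

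**Step 2: variance.** With two time points the interaction is a one-way ANOVA on change, with variance 2σ²(1 − ρ). The ANCOVA residual variance is σ²(1 − ρ²). The ratio is (1 − ρ²)/(2(1 − ρ)) = (1 + ρ)/2.

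**Step 3: power of ANCOVA at the same effect.** λ is divided by (1 + ρ)/2 and multiplied by 55/56 to allow for chance baseline imbalance; df2 = 56. At ρ = 0.5: 12.80/0.75 × 55/56 = 16.77.

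| Assumed ρ | Variance ratio | λ for ANCOVA | Power, interaction | Power, ANCOVA | Total N for ANCOVA to reach 88.7% (equal arms) |
|---|---|---|---|---|---|
| 0.3 | 0.65 | 19.35 | 88.7% | 97.7% | 42 |
| 0.5 | 0.75 | 16.77 | 88.7% | 95.5% | 48 |
| 0.7 | 0.85 | 14.80 | 88.7% | 92.8% | 54 |
| 0.9 | 0.95 | 13.24 | 88.7% | 89.7% | 60 |

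**Step 4: simulation, normal data (6,000 trials per setting).** Interaction against ANCOVA: 89.0% and 97.7% (ρ 0.3), 88.3% and 95.4% (ρ 0.5), 88.7% and 92.6% (ρ 0.7). Type I error of both was 4.5 to 5.4%. Kruskal-Wallis on day-30 values alone had 95.6%, 86.0% and 64.7%.

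**Step 5: simulation, lognormal data with a shift.**

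| Assumed ρ | Interaction | Raw-scale ANCOVA | Kruskal-Wallis on change |
|---|---|---|---|
| 0.3 | 86.1% | 95.5% | 98.2% |
| 0.5 | 84.4% | 92.5% | 98.3% |
| 0.7 | 81.4% | 88.9% | 98.0% |

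Raw-scale ANCOVA still beats the interaction but loses to the rank test. In a separate lognormal simulation rank ANCOVA had about 100% power, against 99.8 to 100% for Kruskal-Wallis on change.

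**Step 6: the normality check.** A Shapiro-Wilk test at n = 20 rejected normality for 18% of samples from a beta(2,5), 18% from a t with 5 df, 29% from a gamma(4) and 53% from a gamma(2). Choosing ANOVA or Kruskal-Wallis on that basis gave type I error of 4.6 to 5.6%, so there was little inflation.

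**The case against.** The strongest reply is that nothing here is an error. The interaction is a valid test, and the article names it only for the sample size; that it is also the analysis is an inference. ANCOVA is itself parametric, so the text does not exclude it. A journal article may leave test names to a full analysis plan. All of this stands, so the missing test names are not the point. What remains is the stated rule that the data pick the branch, and a sample size built on the less efficient use of the baseline.

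A reader might go further in several ways that the article does not support:

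- **The interaction wastes the baseline.** It does not. It uses the baseline with slope 1, matches a day-30-only comparison at ρ = 0.5, and beats it above that (88.7% against 67.4% at ρ = 0.7).
- **The powered test disappears on the nonparametric branch.** It need not. Kruskal-Wallis on change scores is its ready rank counterpart, and the team's own pilot compared change in itching between groups.
- **Raw values, not residuals, will be checked for normality.** The article does not say which quantity is examined.
- **ANCOVA has no downside.** It costs one degree of freedom, assumes a roughly linear baseline slope, and on strongly skewed raw data lost power to the rank test.

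The power figures also describe the 2-df test, not each pairwise contrast. If PBM lay midway between the other two arms, PBM against corticosteroid at ρ = 0.5 would have only about 53% power under ANCOVA: difference 0.566 SD, standard error √0.75 × √(2/20) = 0.274, ratio 2.07.

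**Conclusion.** The point holds as an improvement to a valid but loosely fixed analysis. With roughly normal data, and at the effect implied by the stated power, baseline-adjusted ANCOVA gains about 9 percentage points at ρ = 0.3, 7 at 0.5, 4 at 0.7 and 1 at 0.9. At ρ = 0.5 it would reach the planned power with 48 patients instead of 60. The size rests on assumed correlations and on an 88.7% that cannot be rebuilt from printed inputs; the direction does not depend on either for any ρ below 1, apart from a negligible loss as ρ approaches 1 through the lost degree of freedom.

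The case against the normality check is that the choice of test is unstable at 20 per arm and outcomes may end up analysed by non-comparable methods. A reader might infer that it inflates false positives; in the settings simulated it did so hardly at all, and that claim should not be made.

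**What to change.** Replace the normality-driven choice with one analysis named in advance for each outcome read at baseline and day 30 in all three arms:

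1. **Main model:** day-30 value = arm + baseline value. Report the adjusted between-arm differences with 95% confidence intervals. The aim compares all three treatments, so include PDT against PBM as well as each against corticosteroid.
2. **Outcomes expected to be skewed or ordinal**, such as histology scores and stained-cell counts: name a transformation or rank ANCOVA beforehand as the main analysis, not only as a sensitivity analysis.
3. **Distribution checks:** keep residual plots as description, without letting them switch the main test.

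This changes analysis wording only. It needs no new visits, measurements or patients, and it can be run in the planned software. The cost is one degree of freedom per model and the linear-slope assumption.

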### Global benefits for the patients

The criterion for recurrence will be pruritus, because it is the main patient complaint. The expected optical change in the skin is a reduction in reflection; lichen sclerosus leaves the skin depigmented, i.e. white, which is the color that most reflects. Therefore, as the symptoms diminish, we expect the skin to become less white, meaning that reflection also diminishes. We expect photonic therapies to decrease pruritus as much as the corticosteroid and, in addition, to not decrease the thickness of the skin, avoiding stenosis and pain.

## Discussion

The rare studies of PDT in intraepithelial neoplasia of the vulva have shown increased cytotoxic T lymphocyte in the treated area, as well as reduction in recurrence [27, 28]. The immunological effects of PDT and PBM are also described by several authors in inflammatory skin diseases, stimulating the production and organization of the associated collagen [24, 25, 29]. Thus, it is reasonable to determine the efficacy and safety of these new treatments in vulvar lichen sclerosus, analyzing the recurrence time, the impact on the optical properties of the skin, and the benefit to patients by clinical, histological, immunohistochemical and spectroscopic aspects.

Since high-potency topical corticosteroids are the first line treatment for VLS, clobetasol propionate 0.05% ointment is currently considered the gold standard. Approximately 60% of patients experience complete remission of symptoms, with consequent elimination of fissures, erosions, and hyperkeratosis [15]. Its use is effective, but the atrophy of the skin, scars, and hypopigmentation are irreversible with its use. Typically, a thin layer of steroid (finger tip unit) is applied once or twice daily for 2 to 4 weeks, then being reduced to three times a week, till withdrawal of the product [9].

PDT is a photochemical technique, and has been a treatment option in some gynecological and skin diseases [25, 29]. It consists of a combination of a photosensitizer and a light source, and these must be optically resonant. Its efficacy depends on the selectivity and retention of the photosensitizer, the intensity of the incident radiation, the transfer of excitation energy from the photosensitive agent and its oxidizing effect [30]. Specifically in VLS, its effectiveness has been varied, mainly due to the characteristics of the commonly used photosensitizers (methyl aminolevulinate and 5-aminolevulinic acid), which are topical, requiring periods ranging from two to five hours for sufficient production of porphyrin before the interaction with light [17, 21]. The lack of standardization of the various physical parameters of the radiation (light source, power, exposure time, energy and power densities) also contributes to the partial success of this treatment modality [31]. Adverse effects are reported, such as erythema, burning, and discomfort, even a few hours after therapy. Therefore, the association with intralesional anesthetic is common [17, 21, 31]. Nevertheless, the beneficial effects on the VLS are outstanding, such as the relief of symptoms for up to 6 months and/or the absence of the lesion [16–20].

The few studies of VLS treatments applying PDT are described with 5-aminolevulinic acid, a precursor of the photosensitive agent protoporphyrin IX, or its methyl ester, which is more lipophilic. However, at physiological pH, ALA forms zwitterions, which prevents its ability to cross biological barriers such as cell membranes, resulting in slow and non-homogeneous distribution in the target tissue, even as its high cost and phototoxicity [32].

On the other hand, methylene blue (MB) acting as the photosensitizer makes PDT more reasonable in clinical practice, especially in the Public Health System, since it has a high quantum yield of singlet oxygen and the ability to generate several radical species, it is highly photostable, easily eliminated from the body, presents minimal toxicity and low cost [33]. Moreover, the MB has an affinity for melanin, it is more lipophilic than ALA, actively binds to mitochondria and provides a mechanism for the reduction of the inflammatory response [34, 35]. The monomers and dimers of MB have distinct absorption spectra: the monomers have maximum absorption at 664 nm and the dimers at 590 nm. It is known that in a 20 μM aqueous solution there are only monomers present. A detailed review of the characteristics of MB can be found in the study of Tardivo et al. [36].

In PBM, the power density is not sufficient to induce biological activity dependent on the temperature increase, provided that the recommendations of the World Association for Laser Therapy (WALT) are followed [31]. It can be used with radiation sources that are coherent (lasers) or incoherent (lamps and LEDs). The basic biological mechanism that is currently accepted for explaining, although not completely, the effects observed in PBM is the absorption of red and infrared radiation by chromophores in mitochondria, in particular cytochrome c oxidase, and photoreceptors in the plasma membrane of cells, respectively [30]. The main reported effects are the reduction of pain and inflammation, optimization of tissue repair, tissue and nerve regeneration, and the repigmentation of skin lesions [24]. While these effects are desirable in the treatment of VLS, to date no work has been found associating it with PBM.

Nowadays we know that immunohistochemistry is an indispensable technique for solving differential diagnosis problems caused by basic routine staining of HE [32]. Although we know that the diagnosis of LEV is clinical, we insist to collect the biopsies so that we can cross-check the data (HE versus immunohistochemistry) for a better understanding of the disease and the mechanisms involved after the different therapies. We remember that VLS has a malignant potential of around 4%, and is, therefore, considered as a means of vulvar carcinogenesis, with a recorded incidence of 32% to 76% of squamous cell carcinoma of the vulva adjacent to the lichen area.

Studies performed by different groups has promoted a basis for associating antibodies for IFN-γ (interferon gamma), TGF-β (transforming growth factor beta), CD4, CD8, IL-1 (lymphocyte activating factor), p53, and Ki67 with vulvar lichen sclerosus [3, 5, 13, 33, 34]. The study of these cytokines and proteins will add to the understanding the biological mechanism triggered by photonic therapies.

Cytokine IFN-γ is the major interferon produced by lymphocytes stimulated by mitogens or antigens, and is related to immunoregulation. It is an inducer of IL-2 (interleukin 2), acting on the immune response profile of Th2 cells to Th1 cells, which control the homeostasis of the immune system. There are reports of increased IFN-γ staining in the VLS epidermis compared with the healthy vulva and non-vulvar skin, suggesting that this disease shares the characteristics of a chronic wound [33].

TGF-β protein plays a role in embryonic development, cell differentiation, hormone secretion, and immune function. Specifically during healing, it functions as a chemoattractant for neutrophils, macrophages and fibroblasts [35]. Although no difference has been found in the expression of TGF-β between lichen sclerosus and healthy skin, there are no studies comparing this marker as a function of different therapies, nor of its association with collagen synthesis in VLS [36].

The CD4–CD8 ratio is the ratio of T lymphocytes expressing CD4 antigens to those expressing CD8 antigens. This value is usually assessed in the diagnosis and stages of diseases that affect the immune system. The expression of these markers was pronounced in the dermal infiltrate of VLS [4].

Cytokine IL-1 is a soluble factor produced by monocytes, macrophages and other cells that activates T-lymphocytes and enhance their responses to mitogens and antigens. The biological effects of IL-1 include the ability to meet the requirements of macrophages necessary for activating T cells. The increased expression of this cytokine has also been reported in VLS [33].

Tumor-suppressant protein p53 is a nuclear phosphoprotein encoded by the p53 gene, and its normal function is to control cell proliferation and apoptosis. Ki-67 protein is present only in the active phase of the cell, making it a good marker for cell proliferation. Major expression of both markers was found in VLS, reflecting the risk of progression to malignancy [3, 13].

The demand for performing the challenging task of optically diagnosing and characterizing biological tissues can be attributed to the rapid development of laser applications in the field of medicine and, more recently, the use of LEDs (light-emitting diodes) [37]. Such applications require better understanding of the radiation–tissue interaction, and thus of the optical changes caused by the biological target in the light passing through it (photodiagnostics) and also the optical changes caused by the light radiation in the tissue (phototherapy).

To make inferences regarding the tissue structure based on measured optical characteristics is a complex task. However, the challenge is tempting and promising due to the fact that the optical characterization of biological tissue contains valuable diagnostic information, to the extent that there is a measurable difference between normal and pathological states, including preventively [38].

When the optical properties of the skin are altered, specifically the absorption and scattering coefficients, the intensity of reflectance is affected. The measurement of reflectance spectra has, therefore, been used to obtain the optical characteristics of the skin in vivo [39, 40]. Thus, it is possible to quantitatively evaluate the effect of different agents on skin condition by analysis of the spectral reflectance [41].

There are no reports in the literature on the reflectance of skin affected by VLS, which can contribute not only to the understanding of the mechanisms of the proposed phototherapies, but also to an improved optical knowledge of the tissue as a function of biological changes related to the stage of VLS [42]. Thus, since the spectroscopic study in VLS is unprecedented, it was decided to use reflectance spectroscopy because it is the easiest method in vivo. If significant differences are found between the spectra of different groups or in one patient depending on the duration of treatment, another study will be proposed for more detailed investigation to obtain the reduced absorption and scattering coefficients in the spectral range of the therapeutic window.

## Abbreviations

ECM 1: Extracellular matrix protein
ISSVD: International Society for the Study of Vulvar Disease
LEDs: Light-emitting diodes
MB: Methylene blue
PBM: Photobiomodulation
PDT: Photodynamic therapy
VLS: Vulvar lichen sclerosus
WALT: World Association for Laser Therapy
